### Inclusion/exclusion criteria

Five hundred thirty-eight consecutive patients meeting inclusion/exclusion criteria, undergoing biliary ERCP by two expert endoscopists, will be considered for inclusion.

*Inclusion criteria*:
Patients, ages > 18, with an intact ampulla undergoing ERCP for therapeutic purposes who can provide informed consent. This includes patients who have confirmed choledocholithiasis on imaging and those who have a high suspicion of it based on imaging and lab values. Patients with and without a high suspicion for cholangitis will be eligible for the study. Other indications include the following: other benign biliary duct diseases including strictures, primary sclerosing cholangitis, and Mirizzi syndrome requiring biliary decompression. Furthermore, patients with suspected diagnosis of biliary leak following cholecystectomy will also be considered for enrollment in this study.Ability to read and understand the English language,Ability to follow-up in a reliable manner.

*Exclusion criteria*:
Bleeding disorder (Von Willebrand disorder, platelet count < 100,000, or INR > 1.5),Therapeutic level anticoagulation with low molecular weight heparin (LMWH), warfarin, or a direct-acting oral anticoagulant (DOAC),P2Y12 inhibitors not held for 5 days prior to the procedure,Prior biliary sphincterotomy,Concurrent pancreatitis (with inability to tolerate oral intake and requiring pain management),Altered upper GI tract anatomy (e.g., prior gastric bypass surgery such as Roux-en-Y or Billroth 2 gastrojejunostomy),Inability to achieve adequate sedation,Evidence of malignant infiltration of the ampulla or peri-ampullary area,NFK or standard cannulation is thought not to be feasible.Pregnancy,Operator inability to identify and access the intra-duodenal portion of the bile duct,Presumptive diagnosis of sphincter of Oddi dysfunction,Inability to access intraduodenal segment due to altered anatomy (e.g., ampulla within deep diverticulum),Requirement for pancreatogram or pancreatic intervention,Inability to provide informed consent.

*Recruitment plan:*

Three groups of patients will be approached for consideration of inclusion in this study:
Inpatients at Kingston Health Sciences Centre (KHSC) requiring an ERCP,Clinic patients, for whom an ERCP will be scheduled at a future date,Patients admitted from outside hospitals or out-patients requiring an ERCP.

As per our case series, the first two groups (in-patients and clinic patients) will be identified by the treating gastroenterologist. If the patient is a candidate for the study, the study coordinator will approach the patient and inform them about the background of the study, the risks, the benefits, and answer questions. The signing of the consent form will take place in either the in-patient’s room, a clinic room, or the endoscopy preparation area before the procedure.

Recruitment of the third group of patients (coming directly to KHSC for the ERCP from an outside hospital) will be conducted in a different manner. When the study doctor accepts the referral for the ERCP, the study coordinator will be notified. The study coordinator will meet the patient after they have arrived at KHSC for their procedure and explain the nature of the study, the risks, and benefits, and answer any questions. If the patient is interested, written informed consent will then be obtained before the procedure.

Due to the evolution of the clinical decisions that are made with respect to the ERCP procedure, it may not always be feasible to temporally separate the process of informing a potential participant and consenting a participant. In these exigent circumstances, patients will still be offered the option to participate.

If a participant has formally requested not to participate in research studies, or to be contacted for research purposes/inquires, as indicated in the electronic medical record, they will not be approached for recruitment by the study coordinator.

### Procedure

After obtaining consent, baseline patient characteristics (age, sex, indication for ERCP, preprocedure blood work including ALP, bilirubin, INR, hemoglobin and lipase) and the suspected diagnosis will be documented. The ERCP procedure will follow standard practice for patient preparation, sedation, and intubation of the duodenum. Patients will not be blinded to their treatment group. Patients will receive sedation in the form of midazolam, diazepam, fentanyl, and/or dimenhydrinate. Diclofenac will be administered per rectum at the conclusion of the procedure.

Access to the CBD will be attempted via either NKF or a standard sphincterotome. Upon identification of the ampulla, the operator will evaluate the feasibility of performing both the needle-knife fistulotomy and standard cannulation. If both approaches are feasible, then participants will be randomized with a 1:1 allocation to one of two treatment groups using a central online randomization program (Randomizer for Clinical Trials app, Medsharing, France) and block randomization. The block sizes will not be disclosed to ensure concealment. Should the operator determine that they are unable to safely perform one of the approaches, then the participant will not be randomized. Allocation concealment will be ensured, as the online randomization program will not reveal the treatment group until the endoscopist confirms both approaches are feasible.

To perform the NKF, the ampulla will be identified and closely examined to accurately delineate the infundibulum. A needle knife (Needlecut 3 V, Olympus Medical Canada, Markham, Ontario) will be used to make a 2–3-mm incision in the mid to proximal third of the vertical axis in the intra-duodenal segment of the bile duct. The needle will be used to cut through the mucosa with intermittent examination for the muscular ampullary complex and subsequent penetration into the bile duct usually signaled by bile flow. When bile is seen, the fistula will be gently probed with a guidewire until the CBD is cannulated. Cannulation of the CBD will be confirmed with proximal advancement of the guidewire and contrast injection with cholangiography. If the findings on the cholangiogram indicate that further interventions are necessary, then the fistulotomy site will be extended with the use of standard sphincterotome or balloon sphincteroplasty as per operator. Further interventions include placement of metal or plastic biliary stents, brushing of the ducts for cytology, balloon dilation of strictures, intraductal cholangioscopy basket retrieval of stones, and balloon sweeping of the CBD.

The standard cannulation will be performed using a traditional sphincterotome (Clever-cut 3 V, Olympus Medical Canada, Markham, Ontario) with access gained to the biliary system via the native orifice (group I).

The operator will switch approaches under the following circumstances: [1] the patient was randomized to the sphincterotomy group (group I), but cannulation is not achieved in 10 min or [2] the patient was randomized to the NKF group (group II), but the operator is unable to achieve biliary access and feels they cannot safely cut further.

### Initial data collection and data management

Pre-procedure demographics, as well as lab results of liver enzymes, total bilirubin, lipase, international normalized ratio (INR), hemoglobin, platelets, and the white blood cell count will be recorded. The physician will document any abdominal pain and/or tenderness, both for severity and location. The suspected diagnosis will be documented along with radiologic findings.

Intra-procedure data collection will include total sedation used, sedation start time, endoscope insertion time, visualization of the ampulla, visualization of needle knife or sphincterotome on the screen, time of the sphincterotome making contact with papilla orifice, time of successful cannulation of the bile duct, time for remaining interventions, time of scope out of mouth, and administration of diclofenac. Each procedure will be recorded for verification purposes.

Other data recorded includes the following: ampullary morphology, difficulty of cannulation, normality/abnormality of the CBD, CBD stent placement, cannulation of the pancreas, pancreatic stent placement, pancreatic contrast injection, and any intraprocedural complications.

Post-procedure data will include assessment for pain/ pancreatitis at 24 h post-procedure. If the subject is an inpatient, this will include clinical assessment. If the subject is an out-patient, then they will be contacted by phone and questioned regarding abdominal pain. Should the subject report abdominal pain consistent with pancreatitis, they will be advised to come to the nearest emergency room for assessment as per current standard of care. A post-procedure day 7 phone call will also be scheduled, and subjects will be questioned regarding abdominal pain. Any post-procedure complications will be recorded as previously outlined. Outcome assessors will not be blinded to the treatment group.

Data will be inputted electronically by a full-time research assistant and stored and managed on a secure encrypted program.

### Statistics and sample size

For the sample size calculation, we assume a PEP incidence of 7% with standard cannulation and expect a decrease to 2% in the fistulotomy group. Therefore, 538 patients will be needed (269 in each group) to assess the hypothesis with 80% power and an alpha of 0.05%.

The primary outcome will be assessed in an intention to treat principle. In addition, we plan to report on the number of patients that switched to NKF or standard cannulation following randomization. Primary and secondary outcomes will be assessed using regression methods. A log-binomial model will be used to generate an adjusted relative risk with 95% confidence intervals for the primary outcome. Linear regression models will be used for the secondary outcomes where appropriate. Normally distributed variables are presented as means with standard deviation (SD) and compared using Student’s *t*-test. Non-normally distributed variables are presented as medians with interquartile range (IQR) and compared with the Mann-Whitney-Wilcoxon test. Based on our pilot study, lost to follow-up is not expected to be an issue [21]. For less than 5% loss to follow-up, a complete case analysis will be done. For more than 5% loss to follow-up, multiple imputation and complete case sensitivity analyses (all combinations of the extremes of what could have occurred) will be done. Multiple imputation will be done in SPSS statistical software with all variables missing listed and five imputed datasets will be created.

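### The printed alpha of 0.05% contradicts the plan's own sample size and 95% confidence interval; 269 per group is the size for a two-sided 5% test

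*Protocol article*

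**What the plan says.** All the design figures stand in one paragraph of the protocol article, under Statistics and sample size. For the control group, "we assume a PEP incidence of 7% with standard cannulation"; for the experimental group the authors "expect a decrease to 2% in the fistulotomy group". From these they conclude that "538 patients will be needed (269 in each group) to assess the hypothesis with 80% power and an alpha of 0.05". In the article a percent sign follows the last figure, so the alpha as printed is 0.05%, or 0.0005. Neither sidedness nor an allowance for dropout is given there.

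The next paragraph of the same section sets the primary analysis: "A log-binomial model will be used to generate an adjusted relative risk with 95% confidence intervals for the primary outcome". Under Procedure, "participants will be randomized with a 1:1 allocation to one of two treatment groups". Study design and setting describes a superiority trial with PEP as the primary endpoint. Nothing else in the article restates the alpha or explains why it should be 0.0005.

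**The concern.** An alpha of 0.0005 would be unusual for a single two-arm superiority comparison, and the article gives no reason for it. It also sits beside a 95% interval, which corresponds to a two-sided 5% test. The sample size and the interval therefore imply one threshold, and the printed alpha states another that is 100 times stricter.

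What is at stake is the rule by which the primary result will be called positive or negative. The printed figure is the only significance level the article gives for that test. If it stays, a PEP result with a p-value between 0.0005 and 0.05 is negative by the stated alpha and positive by the stated interval. A reader would have to guess which was prespecified.

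**Working it through.** **Inputs** (Statistics and sample size; Procedure for the allocation): p1 = 0.07, p2 = 0.02, difference 0.05, power 80% (z = 0.8416), 1:1 allocation, 269 per group, no dropout inflation. The mean rate is 0.045. The article does not name its formula; the pooled-variance normal approximation is used here.

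**Formula.** n per group = (z_a × A + z_b × B)² / 0.05², where
- A = √(2 × 0.045 × 0.955) = √0.08595 = 0.2932
- B = √(0.07 × 0.93 + 0.02 × 0.98) = √(0.0651 + 0.0196) = 0.2910

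**Step 1: reproduce the plan's figure.** At two-sided alpha 0.05, z_a = 1.960:
- n = (0.5746 + 0.2449)² / 0.0025 = 0.6717 / 0.0025 = 268.7, so 269 per group and 538 in total, an exact match.
- Power at 269: (0.05 × √269 − 0.5746) / 0.2910 = (0.8201 − 0.5746) / 0.2910 = 0.843, giving 80.0%.

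**Step 2: the alpha as printed.** At two-sided alpha 0.0005, z_a = 3.481:
- n = (1.0205 + 0.2449)² / 0.0025 = 1.6012 / 0.0025 = 640.5, so 641 per group and 1,282 in total.
- Power at 269: (0.8201 − 1.0205) / 0.2910 = −0.689, giving 24.6%.

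**Step 3: could another method reconcile 0.0005 with 269?**

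| Method, 80% power | n per group, alpha 0.0005 two-sided | n per group, alpha 0.0005 one-sided |
|---|---|---|
| Pooled | 641 | 586 |
| Continuity-corrected | 680 | 625 |
| Unpooled | 633 | 579 |
| Arcsine | 590 | 539 |
| Log relative risk | 742 | 678 |
| Log odds ratio | 729 | 666 |

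The smallest figure, 539, is twice the planned group size. Power of 269 per group at 0.0005 runs from 18.5% (continuity-corrected, two-sided) to 31.8% (unpooled, one-sided), with exact power of 24.0% for the two-sided chi-square test and 19.3% for the two-sided Fisher test.

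**Step 4: is two-sided 5% the only match?** One-sided 2.5% is numerically the same test in the favourable direction and also gives 269. One-sided 5% gives 212 (250 with continuity correction). It comes near 269 only with a dropout allowance that the article does not state: 212 / 0.80 = 265, or 250 / 0.95 = 264 rounded up.

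**Step 5: what the expected result would look like.** Expected events are 0.07 × 269 = 18.8 and 0.02 × 269 = 5.4, so about 19 versus 5.
- Pooled z-test: difference 14/269 = 0.0520, standard error 0.0178, z = 2.92, two-sided p = 0.0035.
- Unadjusted Wald test on the log relative risk, closer to the planned model: ln(5/19) = −1.335, standard error √(1/19 + 1/5 − 2/269) = 0.495, z = −2.70, p = 0.007. The 95% interval for the relative risk 0.26 is about 0.10 to 0.69.

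Both p-values are below 0.05 and above 0.0005, and the planned 95% interval excludes 1.

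**The case against.** The strongest reply is that this is a stray percent sign. The size and the interval in the same section both point to 5%, so an informed reader will see what was meant. That stands as an account of the cause, and it limits the consequence: nothing suggests that the trial was designed at 0.0005. It does not remove the error, because a prespecified threshold should not have to be inferred from a back-calculation, and no other part of the article corrects it.

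It may also be said that the missing sidedness is a detail which a condensed article can leave to the full protocol. That is fair. The 95% interval largely settles it, and it is not counted here as a separate defect.

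Two stronger readings are tempting, and the document supports neither.

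- **That the trial really has only about 25% power.** That figure describes the printed threshold. At the level which reproduces the sample size, power is 80.0%.
- **That 538 is a number screened rather than randomised.** Under Inclusion/exclusion criteria the article says "Five hundred thirty-eight consecutive patients meeting inclusion/exclusion criteria, undergoing biliary ERCP by two expert endoscopists, will be considered for inclusion", and patients whose anatomy is found unsuitable at inspection are not randomised. But that sentence concerns patients who already meet the criteria, and the exclusion list covers infeasibility of either technique and failure to reach the intraduodenal segment. The Abstract describes a randomised trial of 538, and the sample size paragraph divides 538 into 269 per group, which only randomised patients can form. The wording is loose, but it does not set a competing target. The article gives no infeasibility rate from which a loss of power could be worked out.

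**Conclusion.** The alpha is wrong as written. At 0.05%, the stated rates and power need 641 per group instead of 269, and 269 per group has about 25% power (about 18% to 32% across methods and sidedness). At two-sided 5%, or equivalently one-sided 2.5%, the planned 269 per group is reproduced exactly. The incompatibility does not depend on the choice of formula; the exact match rests on the pooled normal approximation with no dropout inflation.

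The point is confined to the stated threshold. The sample size is consistent with its assumptions at 5% and needs no change. It deserves correction despite its likely origin as a unit slip, because the expected result itself falls between the two thresholds.

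**What to change.** In Statistics and sample size, replace the alpha of 0.05% with a two-sided alpha of 0.05 (5%). This also settles the sidedness and brings the threshold into line with the 95% confidence interval. Record the correction before the outcome data are analysed, so that the threshold cannot appear to have been chosen afterwards. The cost is one sentence: the sample size, allocation and analysis model all stay as they are.

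### Five imputed datasets leave avoidable Monte Carlo noise: if loss exceeds 5%, a borderline primary p-value could fall either side of 0.05 depending on the seed

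*Protocol article*

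**What the plan says.** All of this stands in the protocol article, Statistics and sample size, unless noted.

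- Below the threshold: "For less than 5% loss to follow-up, a complete case analysis will be done".
- Above it: "For more than 5% loss to follow-up, multiple imputation and complete case sensitivity analyses". The sensitivity analyses are to cover every best-case and worst-case pattern for the missing outcomes.
- The imputation is to be run in SPSS, and "five imputed datasets will be created".
- Expected loss: on the strength of the pilot study, "lost to follow-up is not expected to be an issue". The Discussion also expects it to be low, because PEP appears within days and contact is planned at 24 h and 7 days. Neither place gives a figure.
- Design rates: "we assume a PEP incidence of 7% with standard cannulation and expect a decrease to 2% in the fistulotomy group", with 269 patients per group.
- The primary result is an adjusted relative risk with a 95% confidence interval from a log-binomial model.

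The article does not say outright whether the imputed or the complete-case result is the main one above 5% loss. Listing imputation beside sensitivity analyses makes the imputed result the natural reading.

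**The concern.** The number of imputations is a stated setting here, so it can be judged from this document. The average of a handful of random imputations carries simulation error, and that error is larger when the outcome is rare. At the design rates the trial expects about 19 v 5 PEP events. One or two imputed events more or fewer in the fistulotomy arm visibly shift the log relative risk and its p-value. Two analysts running the same plan on the same data could then report results on opposite sides of 0.05, although nothing about the patients differs. A larger number of datasets reduces this at no cost.

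**Working it through.** **Inputs from the article.** PEP 7% v 2%; 269 per group; 80% power; 1:1 allocation (Procedure); five imputations; trigger above 5% loss, which is 0.05 × 538 = 26.9, so 27 or more patients.

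**Assumed, because the article gives no figure.** Loss of 5.5% or 10% per arm (15 or 27 of 269), and the observed event counts. Results are judged at two-sided 0.05. The article prints the alpha with a percent sign, which is a separate matter; the next step shows which value the sample size uses.

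**Step 1. Reproduce the plan's figure.** With pooled variance and mean rate 0.045:

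n = [1.960 × √(2 × 0.045 × 0.955) + 0.842 × √(0.07 × 0.93 + 0.02 × 0.98)]² / 0.05² = (0.5746 + 0.2449)² / 0.0025 = 268.7, so 269 per group and 538 in all. This matches the article. An alpha of 0.0005 would need 641 per group.

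**Step 2. Expected events.** 269 × 0.07 = 18.8 and 269 × 0.02 = 5.4, about 24 in total. With 10% loss, 242 observed per arm give 16.9 and 4.8, about 17 v 5.

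**Step 3. Simulate the seed.** Hold the observed counts fixed. For each of m datasets, draw the arm's PEP probability from its Jeffreys Beta posterior, draw the missing outcomes, and compute q = ln(RR) and U = 1/x₁ + 1/x₂ − 2/269, where x₁ and x₂ are the completed event counts. Pool by Rubin's rules, T = Ū + (1 + 1/m)B, where Ū is the mean of U and B the variance of q across datasets, with the usual t reference. Repeat for 20,000 seeds.

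**Borderline case: 16 v 6 observed.** Complete-case ln(RR) = ln(6/16) = −0.981, SE 0.470, z = −2.09, p = 0.037.

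| Loss | m | Central 95% of p over seeds | Seeds with p ≥ 0.05 |
|---|---|---|---|
| 5.5% | 5 | 0.023–0.069 | 16% |
| 5.5% | 50 | 0.032–0.044 | about 0% |
| 5.5% | 100 | 0.033–0.042 | 0% |
| 10% | 5 | 0.019–0.087 | 25% |
| 10% | 50 | 0.030–0.047 | 0.6% |
| 10% | 100 | 0.032–0.043 | 0% |

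At 10% loss the seed SD of the log relative risk is 0.065 with m = 5 and 0.021 with m = 50. The ratio agrees with √(50/5) = 3.2.

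**Design-typical case: 17 v 5 at 10% loss.** Complete-case p = 0.014. With m = 5, about 99% of seeds give p < 0.05. The case 19 v 5 at 5.5% loss stays below 0.05 in about 100%.

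**Case very near the threshold: 18 v 8 at 5.5% loss.** Complete-case p = 0.051. The share of seeds below 0.05 is about 46% with m = 5, 39% with m = 50 and still 36% with m = 100.

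**Step 4. Average over trials at 7% v 2%.** Taking 3,000 simulated trials with 100 seeds each, the chance that two seeds give opposite verdicts at 0.05 is:

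| Loss | m = 5 | m = 50 | m = 100 |
|---|---|---|---|
| 5.5% | 4.7% | 1.4% | 0.7% |
| 10% | 7.7% | 1.9% | 1.6% |

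**The case against.** The case against is substantial, and most of it stands as a limit on size.

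- **Validity.** A reader might infer that five datasets make the analysis invalid. They do not. The (1 + 1/m) term in Rubin's rules already carries the simulation error into the standard error. At 10% loss the seed SD of 0.065 is about 14% of an SE of 0.47, or about 2% of the variance (0.14²). The difficulty shows mainly when the result is cut at 0.05.
- **Typical results.** A reader might infer that the trial's conclusion generally hangs on the seed. An example placed on the threshold suggests this: 15 v 6 at 10% loss has complete-case p of about 0.053, and 39% of seeds fall below 0.05 with m = 5. The design's own rates do not support it, as the 17 v 5 case shows.
- **The branch may never be run.** The article expects little loss and gives a reason. This stands, and it makes the point minor.
- **Extreme-case analyses are already planned.** For 16 v 6 with 27 missing per arm, they run from a relative risk of 6/43 = 0.14 to 33/16 = 2.06. They would show a fragile result to be fragile. They do not make the main p-value reproducible.
- **Which result is primary.** The article does not state that the imputed result leads above 5% loss, so the point is conditional on that reading.
- **No random seed is named.** This is commonly left to an analysis plan that is not shown here, so it is not a fault.
- **The model checked is not the planned one.** The planned model is adjusted, and good auxiliary variables in the imputation would reduce the noise.

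**Conclusion.** The point holds in a limited form. The article fixes five imputations, and with about 24 expected events that leaves avoidable noise. If loss exceeds 5% and the imputed analysis is taken as the main result, p-values of roughly 0.03 to 0.06 may change sides of 0.05 by seed. In the 16 v 6 example this affects 16% to 25% of seeds over 5.5% to 10% loss. Averaged over trials at the design rates, two seeds disagree 4.7% to 7.7% of the time. Clear results are not affected. These figures rest on assumed loss fractions and event counts, an unadjusted relative risk, and imputation by arm alone. Severity is minor.

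**What to change.** In Statistics and sample size, replace five with at least 50 imputed datasets; 100 is equally cheap. Going from five to 50 cuts the seed SD of the log relative risk about threefold and makes results near p = 0.037 stable. It narrows the range of seed-dependent p-values but does not abolish it, as the 18 v 8 case shows. The cost is one changed setting and seconds of computing, with no effect on patients, sample size or schedule.
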